#### **3.3. Intervention**

Each site will be allocated to two consecutive periods of a standard protocol of aspirin and a standard protocol of LMWH for VTE prophylaxis with the order of the two periods determined by randomisation at a 1:1 ratio, on an open label basis.

Each site will adhere to the initially randomised protocol for a time period based on surgical volume aiming for 250 patients eligible for the primary analysis per group. The target

recruitment time period for each group will be 12 months, but may extend beyond this if required. Total recruitment (all arthroplasties) to each group is expected to be 300 patients. Patients will be informed of the trial during initial data entry. Patients will be specifically asked at the time of study entry for consent for follow-up, for use of their data in research, and use of linked data to measure and verify surgical outcomes (Appendix 1). Patients will not be individually consenting to be randomised to either aspirin or LMWH, as both drugs represent standard practice and randomisation is not at the patient level. Further details on the consent process is listed in protocol (section 4.3).

Patients will be followed up at 90 (90-120) days and 6 (5-7) months, electronically, with telephone back up. To ensure minimal inconvenience a maximum of three successful reminders will be sent to the patient to complete their follow-up CRISTAL questions. Patients will be contacted beyond 100 days and 6.5 months via telephone, if surveys remain incomplete and if initial telephone contact has not been successful.

- 1st reminder
  - Pre-operative - 2 days after registration
  - 90-day post-operative – 90 days post operation
  - 6-months post-operative - 5 months + 2 weeks post operation
- 2nd reminder
  - Pre-operative - 3 days after the first reminder
  - 90-day post-operative – 95 days post-operation
  - 6-months post-operative – 2 weeks after first reminder
- 3rd reminder
  - Pre-operative - 4 days after the second reminder,
  - 90-day post-operative – 100 days after operation
  - 6-months post-operative – 2 weeks after second reminder

The electronic system used for data collection is also equipped with a Save and Complete feature which will allow an incomplete set of questions to be completed by the patient at a later date.

This was deemed necessary because if a patient is completing a set of questions and they need to stop for whatever reason it is helpful for them to be able to recommence from where they left off. For example, an issue may occur with the internet connection or, if the pre-operative data is being collected in a pre-admission clinic setting, a patient may be called away for different appointments mid-way through completing the questions.

If there is an incomplete set of questions recorded, the patient can log back in at any time within a 2-week period to complete the questions. If the questions are not completed within 48 hours of being started the system will send an additional reminder to the patient prompting them to complete the questions. After 2 weeks the session will be locked and the incomplete set of questions will be utilised.

There will be no change to usual medical follow-up (clinic attendance, investigations etc.) except that routine venous imaging is not to be used (currently not recommended and not commonly used).

Aspirin will be administered orally at 100mg (85-150 mg permitted if previously prescribed) daily for 35 (+/-7) days (hips) or 14 (+/-4) days (knees) commencing the day of or day after surgery.

LMWH will be administered as enoxaparin (Clexane) 40mg subcutaneously daily, for 35 days (hips) or 14 days (knees) commencing within 24 hours of surgery. Patients with renal impairment (creatinine clearance of <30ml/min) will be administered enoxaparin (Clexane) in a reduced dosage of 20mg subcutaneously daily and patients undergoing haemodialysis will be treated according to standard local protocol. The reduced dosage of 20 mg will also apply to patients who weigh less than 50 kilograms. Patients who have a contradiction to either study drug will be treated as per local protocols. If this requires the study drug to be withheld the study site will notify the Registry. Patients will be taught to self-administer while in hospital. For those unable to self-administer, the injections will be given by family members, a community nursing service or their local doctor, depending on local arrangements.

### **3.4. Adherence**

Patients may discontinue the drug if they have an allergy or adverse event related to the drug.

The study drug may be withheld if post-operative wound ooze continues beyond 72 hours post-operatively, with recommencement 48 hours later if settled.

Inpatient adherence during the acute care period will be monitored by an audit of all sites over the first 2 weeks after commencing patient recruitment. A repeat audit will be performed after one month for sites that do not reach at least 80% compliance on the initial audit.

Post-discharge adherence will be determined by patient report during follow-up at 90 days.

### **3.5. Concomitant care**

All patients will have intermittent compression devices intra-operatively and post-operatively until mobile. All patients will be offered mobilisation on day one post-surgery unless surgically or medically contraindicated.

Patients taking (non-aspirin) oral anti-platelet therapy pre-operatively may have their medication withheld for one week pre-operatively if advised by their treating doctor and will recommence their usual medication (in addition to any study medication) at day 7 post-operatively or when safe to do so.

Routine doppler screening for DVT (in asymptomatic patients) will not be permitted by participating sites.

Patients taking aspirin (85-150mg daily) pre-operatively will take this drug in the usual dose post-operatively in place of the study drug for those in the aspirin group, and in addition to

LMWH for those in the LMWH group. The aspirin may be stopped pre-operatively if advised by their treating doctors.

### **3.6. Primary outcome**

The primary outcome is verified, symptomatic VTE (DVT or PE) at 90-day follow-up. All reports of VTE will be verified by contact with treating doctors and institutions. VTE will be deemed verified by the independent Outcome Verification Committee. The absence of VTE will be verified in a random sample of 200 patients reporting an absence of VTE, by auditing treating doctors and institutions. Patients will be asked if they are still taking anticoagulant medication at 90-day follow-up. VTEs will be subclassified into all DVT, below knee DVT, above knee DVT and PE.

### **3.7. Secondary outcomes**

1. Non-VTE complications (see below)
2. PROMs. Health-related quality of life (EQ5D-5L), Oxford hip and knee scores and patient-rated satisfaction and improvement.
3. Costs. If aspirin is found to be inferior to LMWH, the cost of anticoagulation, cost of hospital stay, need for further health resource utilisation (e.g. nurse or GP visits) and complications will be analysed (see list below)
4. Adherence. Proportion of patients taking the drug continuously (no more than 2 consecutive days missed) for the recommended minimum period.

Non-VTE Complications will be classified into the following groups by the Outcome Verification Committee:

- Readmission related to the original surgery or associated treatment (including bleeding and VTE related) within 90 days
- Reason for readmission (infection, dislocation, stiffness, fracture, wound dehiscence, implant loosening, migration or failure, wound bleeding, other bleeding) within 90 days
- Major bleeding events within 90 days ('major' defined as those resulting in readmission, reoperation or death)
- Reoperation on the same joint within 90 days and 6 months
- Type of reoperation (treatment of infection, reduction of dislocation, manipulation under anaesthesia, fracture treatment, wound repair, implant loosening, migration or failure, non-joint related surgery) within 90 days and 6 months
- Death within 90 days and 6 months

All reports of non-VTE complications will be verified by contact with treating doctors and institutions, except for death, which will be verified through the National Death Index (NDI).

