### **2.5. Secondary aims**

- To compare the effectiveness and safety of aspirin to LMWH in preventing symptomatic VTE after all hip arthroplasty (HA) and knee arthroplasty (KA) including primary, revision and partial arthroplasty, performed for any indication including fracture surgery
- To compare the effectiveness and safety of aspirin to LMWH in preventing symptomatic VTE after revision HA and KA
- Compare the safety (proportion of non-VTE complications) between groups
- An extension of the primary analysis for: HA and KA separately; unilateral and bilateral separately; below-knee DVT, above-knee DVT and PE separately
- To compare the cost effectiveness of aspirin to LMWH for VTE prophylaxis after primary elective THA and TKA for osteoarthritis if aspirin is found to be inferior to LMWH

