contraindicated. This will assess the effect of implementing the protocol at a departmental (hospital) level. Other secondary analyses will include an analysis of the subcategories of VTE as the outcome; PE only, all DVT, above knee DVT only and below knee DVT only and non-VTE related complications (death, re-operation, major bleeding and readmission rates). Cluster summary methods will be used for all secondary analyses.

If aspirin is found to be inferior to LMWH, a cost effectiveness analysis of aspirin compared to LMWH will be performed from a health system perspective. Data for resource use associated with treatments and complications will be taken from trial data within the AOANJRR. Survival at one year and quality of life measured using EQ5D at baseline and six months will allow calculation of differences in quality adjusted life years (QALYs) between groups. We will calculate the cost per QALY for each treatment comparison as the difference in mean costs divided by the difference in mean outcomes (quality adjusted survival as QALYs) over the duration of the trial, using regression analysis to adjust for differences at baseline and clustering by site.

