### **Outcome variables**

The primary outcome of the study is symptomatic VTE within 90 days of surgery. Secondary outcomes are:

- Deep vein thrombosis (DVT) only (total, below-knee and above-knee) within 90 days
- Pulmonary embolism (PE) only within 90 days
- Readmission related to the original surgery or associated treatment (including bleeding and VTE-related) within 90 days
- Reoperation on the same joint within 90 days and within 6 months of surgery
- Major bleeding events within 90 days defined as bleeding events resulting in readmission, reoperation or death
- Death within 90 days
- Change in patient-reported pain, function and health status measures as measured by the Oxford Hip Score (OHS), Oxford Knee Score (OKS), EQ-5D score and the EQ-VAS from baseline to 6 months postoperatively

Outcome and demographic data were collected preoperatively (demographics, patient reported pain, function and health status) and at 90 days and 6 months postoperatively. Data for all primary and secondary outcomes are patient-reported (except for death). All patients who responded 'yes' to having experienced a VTE or a secondary operation within 6 months had this result verified by AOANJRR staff through contact with treating doctors and hospitals. A random audit of 200 patients who did not report a VTE event was undertaken to detect the false negative reporting rate. All data collected for registered patients specific to CRISTAL have been outlined in the published protocol [15]. Mortality data were collected through linkage between the AOANJRR and the National Death Index.

In the published protocol [15], mortality was to be measured at 90 days and 6 months. Due to the lack of sensitivity in measuring VTE-related mortality at 6 months, and due to the lag in data availability for mortality, we will only analyse mortality at 90 days [17].

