The secondary outcomes will investigate non-VTE complications (death, re-operation, readmission and major bleeding events) within 90 days, and reoperation and patient-related pain and function at 6 months (OHS, OKS, EQ-5D and EQ-VAS). Cluster summary methods will be used within an intention-to treat approach. For binary outcomes, the cluster mean per period will be the proportion of patients who had the outcome, while for continuous outcomes such as pain score, the cluster mean will be the mean outcome. Treatment effects will be presented as absolute risk differences and 95% confidence intervals to determine if one treatment is superior to the alternative. Results for the secondary outcomes in population 1 will be presented in tabular form (Table 3) and results for the primary and secondary outcomes in populations 2, 3 and 4 in Table 4.

Due to the early stopping of the trial, final analyses of the primary and secondary outcomes will use the same composite method as the interim analyses which accounts for clusters with incomplete as well as no crossover, with 95% confidence intervals. No bias is expected from early stopping if the patients included in the trial are not systematically different from later patients who would have been included after the trial was stopped. Our composite analysis method accounts for clusters which either had incomplete crossover and or did not crossover. However, the lower sample size and unequal cluster sizes decreases the precision of the outcome estimates. Since we used cluster weighted estimates to account for unequal cluster sizes and increased the initial sample size by 27% above the minimum required, the loss of precision will be mitigated. The trial was stopped based on the Haybittle-Peto

boundary of 0.001, so we anticipate the final analysis using 95% confidence intervals will have sufficient power.

**Table 3.** Outcomes for population 1

| Outcome                                            | LMWH Allocation
(n = X) | Aspirin Allocation
(n = X) | Absolute Risk Difference | 95% Confidence Interval | p-value |
|----------------------------------------------------|----------------------------|-------------------------------|--------------------------|-------------------------|---------|
| Any Venous thromboembolism                  | n (%)                      | n (%)                         | X                        | X – X                   |         |

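### Readmission is compared as a non-VTE safety outcome, yet its definition includes VTE-related readmission and no planned analysis separates the two

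*Supplement*

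**What the plan says.** Section 2.5 of the final protocol sets the safety aim: "Compare the safety (proportion of non-VTE complications) between groups". Section 3.7 introduces the list that serves it with "Non-VTE Complications will be classified into the following groups by the Outcome Verification Committee", and the first item is "Readmission related to the original surgery or associated treatment (including bleeding and VTE related) within 90 days". The next item is "Reason for readmission (infection, dislocation, stiffness, fracture, wound dehiscence, implant loosening, migration or failure, wound bleeding, other bleeding) within 90 days"; VTE is not among the reasons. Section 3.15 plans an analysis of "non-VTE related complications (death, re-operation, major bleeding and readmission rates").

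The final SAP keeps both halves. Under Outcome variables the definition is "Readmission related to the original surgery or associated treatment (including bleeding and VTE-related) within 90 days". Under Main analyses the text reads "The secondary outcomes will investigate non-VTE complications (death, re-operation, readmission and major bleeding events) within 90 days", and risk differences with 95% confidence intervals are to be used to judge whether one treatment is superior. Table 3, and each population in Table 4, has a single readmission row.

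The primary outcome covers the same window: "The primary outcome is verified, symptomatic VTE (DVT or PE) at 90-day follow-up".

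**The concern.** An outcome cannot be both non-VTE and inclusive of VTE. As planned, a VTE that brings a patient back to hospital within 90 days counts in the primary outcome and again in a row labelled as non-VTE safety. If one drug has more VTE, its readmission rate rises for that reason alone, and a reader following the labels would take this as worse non-VTE safety. Within that row, extra VTE readmissions on one drug could also offset extra readmissions from other causes on the other.

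The overlap would matter little if VTE rates were equal. The final SAP's Interim analysis section, however, reports that recruitment stopped because a two-sided 0.001 rule on the primary outcome had been met. Equal VTE rates could therefore not be taken for granted when the final SAP was issued (20 July 2021).

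**Working it through.** **1. The passages side by side (latest versions)**

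| Place | Treats readmission as |
|---|---|
| Protocol 2.5 | Safety aim is restricted to non-VTE complications |
| Protocol 3.7, list heading | Non-VTE |
| Protocol 3.7, definition | Includes VTE-related |
| Protocol 3.7, reason list | No VTE category |
| Protocol 3.15 | Non-VTE |
| SAP, Outcome variables | Includes VTE-related |
| SAP, Main analyses | Non-VTE, compared for superiority |
| SAP, Tables 3 and 4 | One undivided row |

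Nothing in either final document removes VTE-related readmissions or reports them separately.

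**2. The plan's own figure**

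The plan gives no figure for readmission. Its sample size is reproduced only to confirm the planning rates and to show that readmission does not enter it. With 2.5% v 1.5%, one-sided 0.025, 90% power and pooled variance:

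- n = [1.960 × √(2 × 0.02 × 0.98) + 1.2816 × √(0.025 × 0.975 + 0.015 × 0.985)]² / 0.01² = 4,117 per group, as stated.
- With intracluster correlation 0.01, interperiod correlation 0.008 and 31 clusters, solve 31m = 4,117 × [1 + (m − 1) × 0.01 − 0.008m]. This gives m = 179.03, rounded up to 180, and 180 × 2 × 31 = 11,160, as stated.

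**3. How much VTE can add to the readmission difference**

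Inputs:
- VTE rates of 2.5% (aspirin) and 1.5% (LMWH), from protocol 3.9.
- f, the share of VTE patients readmitted. This is not in the documents; it is assumed equal in both groups and varied from 0.25 to 0.75.
- r, readmission from other causes. This is not in the documents; it is assumed equal in both groups and varied from 2% to 6%.

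Readmission rate = r + f × VTE rate. With r and f common to both groups, the difference is f × (2.5% − 1.5%) = f × 1.0 point:

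| f | Difference due to VTE alone |
|---|---|
| 0.25 | 0.25 points |
| 0.50 | 0.50 points |
| 0.75 | 0.75 points |

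Example at r = 4%, f = 0.5:
- Aspirin: 4% + 0.5 × 2.5% = 5.25%. LMWH: 4% + 0.5 × 1.5% = 4.75%.
- The 0.5-point difference is all VTE. VTE makes up 1.25/5.25 = 24% of aspirin readmissions and 0.75/4.75 = 16% of LMWH readmissions.

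Over the whole range, the VTE share of readmissions runs:
- Aspirin: from 0.625/6.625 = 9% to 1.875/3.875 = 48%.
- LMWH: from 0.375/6.375 = 6% to 1.125/3.125 = 36%.

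**4. Offsetting within the row**

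At f = 0.5, an assumed 0.5-point excess of bleeding readmissions on LMWH would exactly cancel the 0.5 points that VTE adds on aspirin, and the row would show no difference. Major bleeding is defined in both documents to include bleeding that leads to readmission and has its own row in Tables 3 and 4, so that excess would still be seen there.

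**The case against.** The strongest reply is that this is a matter of labelling. The SAP's Outcome variables list states openly that VTE-related readmission is included, the table row carries no non-VTE label, and surgery-related readmission of any cause is a legitimate outcome in a pragmatic trial. The size is illustrative: f has no source in the documents, 2.5% v 1.5% is a gap equal to the full non-inferiority margin and not an expected effect, and with equal VTE rates and equal f the distortion is zero.

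Much of that stands. What remains is that readmission is assigned to the non-VTE safety aim and compared for superiority. No other readmission row answers that aim, so the label decides how the result is read.

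A reader might also infer three stronger things that the documents do not support:

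- **That the whole primary outcome is counted again in a safety composite.** Only VTE events that led to readmission overlap; VTE found during the index stay or managed without readmission does not. No composite is specified.
- **That a bleeding excess could be hidden.** The major bleeding row keeps it visible; any netting out is confined to the readmission row.
- **That the reason codes already collected would separate the cases.** The listed reasons have no VTE category, so tabulating them would not isolate VTE readmissions.

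**Conclusion.** The contradiction is real and stands in the latest version of both documents. As written, a difference in VTE can appear as a difference in non-VTE safety. VTE alone would contribute 0.25 to 0.75 points to the readmission difference, given the planning rates, a readmitted share of 25% to 75% common to both groups, and equal readmission from other causes. Only the VTE rates come from the plan. The primary analysis, its significance level and the sample size are untouched. This should be corrected because it affects how a secondary safety result is interpreted; it does not threaten the trial's main conclusion.

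**What to change.** - In Tables 3 and 4, add a row for readmission not related to VTE, and use it for the safety aim in protocol 2.5.
- Identify these readmissions by matching each one to the verified VTE records. Write down, before allocation is unmasked, how it is decided that a VTE was the cause.
- Add VTE to the list of readmission reasons in protocol 3.7.
- Keep all surgery-related readmission as its own row, without the non-VTE label.
- Bring protocol 2.5, 3.7 and 3.15 and the SAP's Outcome variables and Main analyses sections into line.

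The cost is one extra row per population and a cross-check against VTE data already held, with some judgement of cause for matched cases. At the least, the non-VTE label should come off readmission. Death overlaps with VTE in a similar way, but protocol 4.5 says the death-index linkage gives fact of death only, so death cannot be split by cause from that source.

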### 3.8. Participant timeline

| Time Point    | Data Collection Questions and Instruments                                                                                                                                                                                                                                                                                                      |
|---------------|------------------------------------------------------------------------------------------------------------------------------------------------------------------------------------------------------------------------------------------------------------------------------------------------------------------------------------------------|
| Pre-operative | Current anticoagulation use (yes/no and drug)
History of previous VTE
Age
Sex
Joint (hip or knee)
Side
Unilateral vs bilateral
Primary or revision
ASA grade
BMI
Oxford Hip or Knee Score
EQ-5D-5L
EQVAS
Low back pain
Joint pain (numeric rating scale 0-10)
Expectations (pain and improvement) |
| 90 days       | VTE (DVT or PE)
Adherence (did you use pills or injections to prevent a blood clot post-operatively, for how long?)
Current use of anticoagulants (yes/no, which one)
Complications (asked individually, as per complication list)                                                                                                    |
| 6 months      | Complications (asked individually, as per complication list)
Oxford Hip or Knee Score
EQ-5D-5L
Joint pain (scale 0-10)
Satisfaction with outcome of surgery
Patient-rated improvement                                                                                                                                           |

